### Study participants

The recruitment of participants for this RCT is based at Hamad General Hospital. Patients who will undergo bariatric surgery and fulfill our inclusion and exclusion criteria will be randomized to either the intervention or the control arm of the study. The catchment area for Hamad General Hospital can include the entire Doha district and the surrounding metropolitan areas. However, admission to the hospital may also include other regional areas, thereby making the sample of our population representative of the entire Qatari population.

### Inclusion criteria

Study participants had the following criteria in order to participate in the trial:Qatari males or females.Aged between 18 and 60 yearsBased at the bariatric surgery list of Hamad Medical Corporation (HMC) with their follow up scheduled be at HMC (see appendices).Patients who consent to participate in the 6 months trial

### Exclusion criteria

Patients will be excluded from participating in the trial if they have the following criteria:Any Renal or liver disease because that may affect protein or albumin level in body.Past history of bariatric surgery (Gastric Band & Gastric bypass)Patients will be further excluded after starting the trial if they did not take at least 80% (minimum 24 bottles per month) of their allocated intervention or placebo products throughout the trial.

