## Abstract

**Background:**

Severe weight loss through means of bariatric surgery has been associated with loss of muscle mass due to lack of absorption of protein. The aim of this RCT is to investigate the effectiveness of protein supplementation in reducing the risk of developing protein malnutrition and muscle wasting in post-bariatric surgery patients in Qatar.

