**Methods and analysis:**

The study was based at the Department of bariatric and metabolic surgery, Doha metropolitan and regional areas. It is envisaged that approximately 160 post-bariatric surgery patients will be randomized and followed up for 6 months. These will be males and females obese (BMI >35) Qatari patients between the aged 18–60 years. Subjects with renal or liver disease and those with past history of bariatric surgery will be excluded. By the completion of the trial, patients who took less than 80% of the supplement will be further excluded from the final analysis. Protein supplement (Cubitan,Protein, Nutricia, Netherlands) that contain daily intake of 20 g of protein to be taken orally 3 times a day throughout the study period. The placebo group will receive identical ampule containing zero-protein with exact instructions as per the intervention group. Body weight, muscle and fat mass, total protein, albumin, vit B12, Magnesium and Zinc will be measured at baseline and every follow up/study visit. Study variables will be compared between the 2 groups at different stages of the trial, including baseline, using Sample T-test (paired and unpaired) and the significance level will be confirmed with the 95% confidence interval with alpha error set to 0.05.

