**Strengths and limitations of this study:**

One major strength of our study is that our population is a distinctive population (Qatari Obese patients) where results from international studies may not apply to the local and unique context. A local study like ours will provide healthcare providers in Qatar an opportunity to ensure good clinical practice and healthy and sustainable weight loss following bariatric surgery.

The well-designed double-blinded RCT will almost certainly provide us with the evidence-based clinical practice guideline that we seek as health professionals.

One limitation of our study is the slight discrepancy in caloric content of the intervention and the placebo (250 cal and 100 cal, respectively). However, it is the intervention that has the higher caloric content, in which case it may not influence the results in the direction of our hypothesis that protein supplementation leads to lower fat mass and higher muscle mass.

Another limitation is that the use of the intervention and the placebo are not objectively measured. However, all efforts will be made to ensure compliance and reporting of consumption of products.

A third limitation could be loss to follow up. Participants may cease to participate, particularly, once they have lost “sufficient’ weight and gained the fitness to consume any type of foods they desire. This is common in late stages of post-bariatric surgery (beyond 3 months). We feel that this may be a challenge, particularly in reference to our specific population. However, such findings albeit negative, should serve in improving the clinical practice delivered by healthcare providers.

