## Statistical analysis

Data analyses will be performed using the statistical software SPSS package 23. The main aim is to analyze Body composition and other anthropometric changes throughout the follow up. The normality of the variables will be assessed by the Kolmogorov-Smirnov test. Non-parametric tests will be used in case of non-normal distributions of variables. Characteristics and demographics of participants will be summarized, based on the assignment of treatment or placebo, using means and standard deviations (SD) for quantitative variables. Baseline data for the two groups will be compared using two tailed independent samples t-tests and the *P* value of this difference for each variable will be provided. During the follow-up, changes in weight, body fat percentage, muscle mass, total protein level, albumin level, vit B12, Zinc and Magnesium will be compared within groups using paired t-test and between groups using independent sample t-test. In the case of non-normal distribution of variables, any two independent (unpaired) samples Student’s t test will be replaced by Mann-Whitney U test. However, in the case of Two dependent (paired) samples Student’s t test, Wilcoxon signed rank (paired samples) test will be used. A multiple linear regression model will also be conducted to adjust for age and gender will be conducted. Other fundamental confounders such as diet intake are not incorporated into the multiple binary regression model. This is primarily because post-bariatric patients within the 1st few months (early post-operative phase) are both unable and not allowed to take any solid foods and few specific liquid foods such as milk and soups are recommended to them by the dietician. All patients are trained to follow such diet. Moreover, being an RCT, it is expected that all confounders (including hidden confounders) are balanced between the 2 groups and no assessment of baseline variables such as diet, physical activity and any other biological differences between the 2 groups is required. This is consistent with the CONSORT statement for RCTs.

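### Randomised patients who report taking under 80% of their product are dropped from the final analysis, so the groups compared are no longer the randomised groups

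*Protocol article*

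**What the plan says.** The Exclusion criteria list, after renal or liver disease and previous bariatric surgery, a condition that can only be met after randomisation: "Patients will be further excluded after starting the trial if they did not take at least 80% (minimum 24 bottles per month"). It applies to both products. The abstract (Methods and analysis) ties the rule to the analysis: "By the completion of the trial, patients who took less than 80% of the supplement will be further excluded from the final analysis". The Sample size section is consistent with this, because it counts non-compliance together with dropout and loss to follow-up when raising 130 patients to 160. No other analysis population is named.

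Four other statements bear on the rule:

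- **Measurement of intake.** Strengths and limitations concedes that "the use of the intervention and the placebo are not objectively measured". Study visits describes weekly telephone questions, a patient diary and hospital forms.
- **Balance.** Statistical analysis argues that, "being an RCT, it is expected that all confounders (including hidden confounders) are balanced between the 2 groups", and concludes that baseline diet, physical activity and biological differences need no assessment.
- **Adjustment.** The same section says: "A multiple linear regression model will also be conducted to adjust for age and gender".
- **Stopping.** Strengths and limitations expects loss to follow-up: "Participants may cease to participate, particularly, once they have lost" what they regard as enough weight. It adds: "This is common in late stages of post-bariatric surgery (beyond 3 months").

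**The concern.** Randomisation makes the two groups comparable at the moment of allocation. Selecting patients afterwards on how much product they took gives up that guarantee, because intake can depend on the product itself and on how the patient is doing.

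Both are plausible here. Under Intervention and Control, the active bottle holds 20 g protein and 250 kcal; the placebo holds no protein, no fat and 100 kcal. Tolerance and willingness to continue could therefore differ by arm. The article also expects patients to leave once they have lost enough weight, and weight loss is closely tied to fat and muscle mass, the primary outcomes.

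At stake is the meaning of the primary result. A difference in muscle or fat mass among compliers could reflect who was kept and not what the protein did. Adjusting for age and gender would not separate the two. The article's stated aim, to "investigate the effectiveness of protein supplementation in reducing the risk of developing protein malnutrition and muscle wasting", is also more naturally served by the effect of offering the supplement to patients, some of whom will stop.

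**Working it through.** **1. The cut.** Inputs: one bottle a day (Intervention; Control), 24 bottles a month (Exclusion criteria), 6 months. With 30-day months, 24/30 = 80%, so the plan's own figure reproduces. Over the trial, 6 × 30 = 180 bottles and 0.80 × 180 = 144. At full intake, bottle 144 is reached at 144/30 = 4.8 months.

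The rule can be read as a minimum in every month or as a total. A total below 144 fails both readings, because six months of at least 24 bottles cannot sum to less than 144. The monthly reading is stricter: one poor month could exclude a patient.

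**2. Patients who stop the product once they have lost enough weight.** Assume every bottle is taken until stopping.

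- Stop at 3 months: 90/180 = 50%, excluded.
- Stop at 4 months: 120/180 = 67%, excluded.

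The article speaks of ceasing to participate; that the product is stopped at the same time is my assumption.

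**3. How large could the bias be?** The documents give no exclusion rates, so this is only an illustration. Assume no true effect, 80 per arm, outcome SD 1, and a latent tendency to adhere that has correlation r with the outcome in both arms. If the lowest fraction p of an arm is excluded, the mean outcome of those kept shifts by r × φ(z_p)/(1 − p), where z_p is the normal p-quantile. The bias is the difference between the arms' shifts. Its standard error is √(1/[80(1 − p_A)] + 1/[80(1 − p_B)]).

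| Excluded, arm A v arm B | r | Bias (SD) | Type I error |
|---|---|---|---|
| 10% v 10%, or 20% v 20% | 0.2 to 0.6 | 0 | 5.0% |
| 20% v 10% | 0.2 to 0.6 | 0.03 to 0.09 | 5.4% to 8.4% |
| 30% v 10% | 0.2 to 0.6 | 0.06 to 0.18 | 6.3% to 17.4% |

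Example, 30% v 10% with r = 0.6: 0.6 × (0.3477/0.7 − 0.1755/0.9) = 0.18 SD.

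**4. What an as-assigned analysis does to power.** Inputs from Sample size: 90% power, 5% type I error (taken as two-sided), 130 patients raised to 160. The allowance is (160 − 130)/160 = 18.75%.

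At n = 130 the expected test statistic is 1.960 + 1.2816 = 3.2415. With N patients measured and the effect diluted by a fraction d, it becomes 3.2415 × (1 − d) × √(N/130). Power is the normal probability below that value minus 1.960. Here d is the non-adherent share, assuming those patients get no benefit.

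| N measured | d | Expected statistic | Power |
|---|---|---|---|
| 160 | 0 | 3.596 | 94.9% |
| 160 | 10% | 3.237 | 89.9% |
| 160 | 18.75% | 2.922 | 83.2% |
| 160 | 30% | 2.517 | 71% |
| 144 | 10% | 3.070 | 86.7% |

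Break-even dilution for 90% power is 1 − √(130/160) = 9.9% with 160 measured, and 1 − √(130/144) = 5.0% with 144.

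These figures take the 130 at face value. It does not follow directly from the quoted means and SDs. Using n per arm = 2 × 3.2415² × SD²/difference², the follow-up fat-mass difference of 6.0 kg (SD 13.37) needs 105 per arm and the lean-mass difference of 4.0 kg (SD 10.96) needs 158. The table therefore shows relative changes, not the trial's actual power.

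**The case against.** The strongest reply is that the trial is double-blind with identical bottles, and that one pre-stated rule applies to both arms. The illustration above bears this out in part: equal exclusion with the same selection in both arms gives no bias. But blinding does not make the two drinks equally tolerable, and equal exclusion rates suffice only if the reasons for stopping also match. The risk is lowered, not removed.

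Other points carry some weight:

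- The Primary objective compares participants who received each product, which fits a by-receipt comparison. The wording of the aim in the abstract does not settle the target of estimation on its own, and I put little weight on it.
- The remark on stopping concerns loss to follow-up. A patient who leaves altogether may have no 6-month trial measurement under either analysis, so removing the rule recovers little for that patient. It matters for those who stop the product but can still be measured.
- The plan does compare baseline data between groups. That can reveal imbalance in the variables measured, but the same section declares assessment of diet and activity unnecessary and adjusts only for age and gender.
- An as-assigned analysis costs power if non-adherence is common or follow-up incomplete: 86.7% with 144 measured and 10% non-adherent, 71% with 160 measured and 30% non-adherent.

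None of this rescues the rule. A per-protocol analysis is legitimate as support, but here it is the only final analysis stated. Nor is it a detail left to an unseen analysis plan, since the article itself fixes it.

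**Conclusion.** The concern holds. The only stated final analysis removes randomised patients on the basis of self-reported intake after randomisation, and the article's own argument for balance does not carry over to the remaining subset. This follows from the text and does not depend on the sample size or on any figure above.

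The number excluded and the size and direction of bias cannot be derived from the documents. What is certain is that, with 180 daily bottles, a patient who takes fewer than 144 is excluded on either reading. That outcome-related stopping triggers the rule, and that exclusion differs by arm, are plausible from the article but not shown. The bias and power tables rest on the assumptions stated with them.

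A lesser point is that the wording under Exclusion criteria could also be read as removal during the trial, which might lose later measurements. Exclusion at the end is the likelier reading. The rule should be changed, and preferably settled while follow-up can still be collected.

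**What to change.** - Delete the post-start intake condition from Exclusion criteria and the matching exclusion from the abstract.
- State that low intake or stopping the product does not end participation, and that all randomised patients are to be measured at 1, 3 and 6 months.
- Make the primary comparison of change in muscle and fat mass in all randomised patients, as assigned.
- Keep the 80% cut for a supportive per-protocol analysis only, defined once as total bottles over 6 months (144 of 180).

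The cost is protocol wording plus some effort to follow patients who stop the product; Measurements describes these assessments as routine care. The estimated effect may be smaller than among compliers. Taking 130 at face value, power stays at about 90% or more if all 160 are measured and dilution is at most about 10%. It falls to about 83% if the whole 18.75% allowance is non-adherent, and lower still if non-adherence exceeds that or measurements are missing.

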### Sample size

The study population are bariatric patients admitted to bariatric department for surgery based on their eligibility criteria (BMI ≥ 35). All patients will be enrolled in the study prior to admission and will be given the intervention or the placebo on the first day post-surgery, depending on their randomization. A total of 160 obese Qatari adults from Bariatric and Metabolic Center in Hamad General Hospital (HGH), who fulfill HGH entry criteria for bariatric surgery, are expected to be enrolled in this experimental study.

Using the primary outcome estimates available in the published study (Schollenberger, A E et al.; 2016), body fat mass (BFM) and lean body mass (LBM) (kg) in the intervention group at baseline, 3 and 6 months (BFM baseline 78.2 ± 19.1, 3 and 6 months 59.9 ± 15) and (LBM baseline 65.2 ± 14.2, 3 and 6 months 58.2 ± 10.6) compared with Placebo group (BFM baseline 68.2 ± 12.0, 3 and 6 months 53.9 ± 11.5) and (LBM baseline 68.9 ± 13.4, 3 and 6 months 62.2 ± 11.3). Considering a 90% power and a type I error rate of 5%, the required sample size would be 130 participants (65 in each group), however, to compensate for possible dropouts, non-compliance and loss to follow-up an additional 15% to 20% will be added to the above sample size (a total of 160 participants i.e., 80 in each group). The only difference between the above study population and the population of our RCT is that the German study population were more obese (BMI between 49 and 52). Both studies looked at the effect of protein supplementation on muscle and fat mass in post-bariatric surgery patients.

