### Study objectives

#### Primary objective

To estimate the difference in change of muscle and fat mass between participants who received protein supplement and those who received the placebo.

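### The quoted planning data do not yield 65 per group at 90% power for the difference in change: lean mass shows no favourable effect, and fat mass needs an unstated correlation of about 0.9

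*Protocol article*

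**What the plan says.** The Primary objective section of the protocol article sets the estimand: "To estimate the difference in change of muscle and fat mass between participants who received protein supplement and those who received the placebo". The Statistical analysis section compares changes between groups with an independent-samples t-test.

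The Sample size section presents fat mass and lean mass from a cited study as its primary outcome estimates. For lean mass it gives "LBM baseline 65.2 ± 14.2, 3 and 6 months 58.2 ± 10.6" in the intervention group and "LBM baseline 68.9 ± 13.4, 3 and 6 months 62.2 ± 11.3" in the placebo group, with matching figures for fat mass. It then states: "Considering a 90% power and a type I error rate of 5%, the required sample size would be 130 participants (65 in each group". The total is raised to 160 to cover losses.

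The article does not say which contrast, target difference, SD of change or sidedness lies behind 65. The only mention of a two-tailed test concerns baseline: "Baseline data for the two groups will be compared using two tailed independent samples t-tests".

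**The concern.** The paragraph gives inputs, error rates and a result, so the result can be checked. Read against the primary objective, the inputs do not lead to it.

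For one of the two primary components the quoted difference in change is close to zero and runs against the hypothesis in the Strengths and limitations section, which is lower fat mass and higher muscle mass with protein. For the other, the result depends on a quantity that the article does not give.

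The stated power is what readers will use to judge how informative a null result is. As written, 90% appears to cover both components. Preventing muscle wasting is the stated motivation of the trial, and that is the component for which the quoted data offer no support.

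**Working it through.** **Inputs** (Sample size section; kg, mean and SD)

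| | Baseline | 3 and 6 months | Change |
|---|---|---|---|
| Fat, intervention | 78.2 (19.1) | 59.9 (15) | -18.3 |
| Fat, placebo | 68.2 (12.0) | 53.9 (11.5) | -14.3 |
| Lean, intervention | 65.2 (14.2) | 58.2 (10.6) | -7.0 |
| Lean, placebo | 68.9 (13.4) | 62.2 (11.3) | -6.7 |

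Alpha is 5% and power 90%. Two-sided testing is assumed, as is one correlation r between baseline and follow-up, the same in both arms. Power and sample sizes use the two-sample t-test; for the fat-mass and follow-up sizes below, the normal approximation gives one fewer per group.

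**1. What 65 per group means.** By the normal approximation, the detectable standardised difference is d = (1.960 + 1.282) × √(2/65) = 0.569; by the t-test it is 0.573. So 65 per group gives 90% power for a standardised difference of about 0.57.

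**2. Difference in change.** Fat: 18.3 − 14.3 = 4.0 kg more loss on protein, in the hypothesised direction. Lean: 7.0 − 6.7 = 0.3 kg more loss on protein, against it.

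**3. SD of change.** In each arm the variance of change is s₀² + s₁² − 2·r·s₀·s₁, then averaged over arms. Example, fat at r = 0.8:
- intervention: 364.81 + 225 − 458.4 = 131.41
- placebo: 144 + 132.25 − 220.8 = 55.45
- SD = √((131.41 + 55.45)/2) = 9.67

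| Assumed r | Fat: SD of change | Fat: power at 65 | Fat: n per group for 90% | Lean: SD of change | Lean: power at 65 | Lean: n per group for 90% |
|---|---|---|---|---|---|---|
| 0.7 | 11.66 | 49% | 180 | 9.96 | 5% | over 23,000 |
| 0.8 | 9.67 | 65% | 124 | 8.31 | 5% | over 16,000 |
| 0.9 | 7.14 | 89% | 68 | 6.24 | 6% | over 9,000 |
| 0.95 | 5.45 | 99% | 41 | 4.88 | 6% | over 5,500 |

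**4. What would reproduce 65 for fat mass.** The SD of change must be 4.0/0.573 = 6.98 kg. The averaged variance is 433.03 − 424.5·r. Setting this to 6.98² = 48.7 gives r = (433.03 − 48.7)/424.5 = 0.905. With a one-sided test, the normal approximation gives 78 per group at r = 0.85 and 55 at r = 0.9, so a high unstated correlation is still needed.

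**5. Follow-up values instead of change.**
- Fat: 6.0/13.37 = 0.449, so 106 per group; power at 65 is 72%.
- Lean: 4.0/10.96 = 0.365, so 159 per group; power at 65 is 54%.

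Neither gives 65. One-sided at 90% power the figures are 85 and 129 (normal approximation). Fat mass at follow-up comes near (62) only with a one-sided test and 80% power, which contradicts the stated 90%.

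**6. What 65 evaluable per arm can detect at 90% power.**
- Fat: 0.573 × 6.98 = 4.0 kg (r about 0.9); 0.573 × 9.67 = 5.5 kg (r = 0.8).
- Lean: 0.573 × 6.24 = 3.6 kg (r = 0.9); 0.573 × 9.96 = 5.7 kg (r = 0.7).

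**The case against.** The strongest defence concerns fat mass. The 4.0 kg difference in change matches the estimand and the hypothesised direction, and it reproduces 65 per group at a correlation of about 0.9. The authors may have had such a value, and a condensed article may leave the SD of change to the full protocol. This stands: the missing detail alone is no fault, and 65 cannot be called wrong for fat mass.

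Second, the 5-6% figure is power for the difference seen in the quoted data, not for a target the authors chose. A reader might infer that the trial has no useful power for muscle mass at all. The document does not support that: 65 per arm has 90% power for a lean-mass difference of about 3.6 to 5.7 kg under the correlations shown. What remains is that the article derives its size from these data, and they point to no such effect. Lean mass is also only a stand-in here, since the Body composition section lists fat-free mass and estimated muscle mass as separate outputs.

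Third, a reader might take 106 and 159 per group as the sizes the trial needs. They are not a corrected target. The follow-up gaps run against the hypothesis (fat 6.0 kg higher and lean 4.0 kg lower on protein) and largely carry over baseline gaps of 10.0 and 3.7 kg; they are also not the change estimand.

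Finally, it would be wrong to say that no outcome is named, because the paragraph identifies fat and lean mass as the primary outcomes.

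**Conclusion.** The point holds in a limited form. The 90% claim, stated without qualification for 65 per group, does not follow from the quoted data for the difference in change. For lean mass those data give a 0.3 kg difference against the hypothesis and about 5-6% power for it at any correlation up to 0.95, so they support no favourable muscle target. For fat mass the claim is unsupported but not disproved, since it holds if the correlation is about 0.9.

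This rests on a two-sided 5% test, a common correlation in both arms, and the figures as quoted in the article; the cited study itself was not examined.

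The step from 130 to 160 is not part of this point. A reader might see an error in "an additional 15% to 20% will be added to the above sample size", because 130 plus 20% is 156. Read as an allowance for loss, however, 130/0.85 to 130/0.80 is 153 to 163, which contains 160; the wording is loose at most.

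**What to change.** Replace the unqualified 90% statement in the Sample size section with what the design delivers:

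- State that 65 evaluable per arm gives 90% power, two-sided 5%, for a standardised difference in change of 0.57.
- For fat mass, state that this is 4.0 kg if the SD of change is 7.0 kg (assumed correlation about 0.9) and about 5.5 kg if it is 9.7 kg (assumed correlation 0.8). If the authors hold an SD of change, give it with its source.
- For lean mass, state that this is about 3.6 kg (assumed correlation 0.9) to 5.7 kg (assumed correlation 0.7). Label it a chosen target, and say that the lean-mass figures quoted in the section do not support an effect of that size.

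The cost is one rewritten paragraph and a less favourable stated power. No patients are added.
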